Box 1Overview of inclusion and exclusion criteriaInclusion criteriaAge ≥55 years and ≤75 years old.Living in a postal code area ranked as equal to or less than the lowest third decile of IMD*.Good proficiency of the national language (English in UK and Mandarin in China).Possession of a smartphone.≥ Two dementia risk factors:Insufficient physical activity (self-reported intermediate or vigorous activity of <150 min per week).Active smoking (self-reported use of any sort of tobacco in any quantity).Depression (by meeting at least one of the following criteria):Current diagnosis by specialist or GP.History of treatment for depression (ie, drug therapy or psychotherapy).Manifest cardiovascular disease, as diagnosed by specialist or GP.Diabetes mellitus (by meeting at least one of the following criteria):Diagnosed by specialist or GP.Use of insulin or other blood glucose-lowering medication.Hypertension (by meeting at least one of the following criteria):Diagnosed by specialist or GP.Use of blood pressure-lowering medication.Mean of baseline blood pressure measurements of ≥140 (systolic) or ≥90 (diastolic).Obesity (by meeting at least one of the following criteria):BMI ≥30 (UK) and ≥28 (China).Baseline waist circumference ≥102 cm (men in UK), 90 cm (men in China), 88 cm (women in UK) and 85 cm (women in China).Dyslipidaemia (by meeting at least one of the following criteria):Diagnosed by specialist or GP.Use of lipid-lowering medication.Baseline total cholesterol ≥5.0 mmol/L*.Exclusion criteriaManifest dementia, as diagnosed by specialist or GP.MMSE <24 (participants with ISCED level of >1) and MMSE <21 (participants with ISCED level of 1).Any condition expected to limit 18-month follow-up, including metastasised malignancy or other terminal illnesses.Smartphone illiteracy, defined as not being able to send a message from a smartphone.Visual impairment interfering with operation of a smartphone.Participating in another RCT on behaviour change.Present severe alcohol or illicit drug abuse.* Applies only to participants in the UKBMI, Body Mass Index; GP, general practitioner; IMD, Index of Multiple Deprivation; ISCED, International Standard Classification of Education; MMSE, Mini-Mental State Examination; RCT, randomised controlled trial.

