### Primary and secondary outcomes

Following a type II hybrid design, primary outcomes for effectiveness and implementation are equally important. The primary effectiveness outcome is the change in the Cardiovascular Risk Factors, Ageing and Incidence of Dementia (CAIDE) dementia risk score between baseline and 18-month follow-up.^31^ The main secondary effectiveness outcomes include change in the individual modifiable components of the primary outcome, change in ten-year cardiovascular disease (CVD) risk, cost-effectiveness and certain clinical outcomes such as incidence of mild cognitive impairment (MCI) and dementia. The operationalisation of all effectiveness outcomes is listed in table 1.

**Table 1 T1:** Effectiveness outcomes

Primary outcome	Points
CAIDE Score (range: 0–15), which is composed of and calculated from the following:	
Age	
<47 years	0
47–53	3
>53	4
Education	
≥10 years	0
7–9 years	2
<7 years	3
Gender	
Female	0
Male	1
Systolic blood pressure	
≤140 mm Hg	0
>140 mm Hg	2
BMI	
≤30 kg/m^2^	0
>30 kg/m^2^	2
Total cholesterol	
≤6.5 mmol/L	0
>6.5 mmol/L	2
Physical activity*	
Yes	0
No	1

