### Statistical analysis

#### Sample size

The CAIDE Score will be used as primary effectiveness outcome. We decided to use a difference of 0.186 points on the CAIDE Score between the average of both study groups as a minimum target threshold, because this difference was observed in the Prevention of Dementia by Intensive Vascular Care trial after 2 years (p=0.005; intervention group=−0.290±1.47 SD and control group=−0.104±1.36 SD). Attrition after 2 years of follow-up was 21% in this study.^14^ With 80% power, a 0.05 two-sided significance level, accounting for 21% attrition, and a mean difference in change in CAIDE of 0.186, the required sample size is estimated to be 2319 participants. To allow for unexpected factors, we raised this to 2400.

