#### Data analysis

The effect on the CAIDE Score will be analysed using linear mixed-effect models according to the intention-to-treat principle, taking clustering within partner pairs and country into account by testing best fit for random intercept and/or slope. If needed, we will adjust for baseline imbalances and take clustering of the intervention within centre and/or coach into account. No imputation of the CAIDE Score will be done for the primary analysis. In sensitivity analyses, we will use multiple imputation to assess the impact of missing items needed to calculate the CAIDE Score, provided there are no indications that the variables are missing not at random, and a per-protocol analysis for those adherent to the intervention will be performed. Moreover, we will explore the interaction of intervention duration with the effect of the invention by adding an interaction term (intervention duration*randomisation group) to the main model. This will give insight into the potential additional intervention effect in participants with a follow-up time of less than 18 months.

Subgroup analyses will be performed for country, sex, age group, having a history of CVD, number of risk factors, willingness to change lifestyle (assessed with one question during the baseline visit), participation with(out) a participating partner, having the same coach during the full length of the study and the number of goals set. For all these factors, interaction terms will be included to test for between-subgroup differences in intervention effects.

The effect on individual modifiable components of the CAIDE Score and 10-year CVD Risk Scores will be analysed using linear mixed-effect models according to the intention-to-treat principle, taking clustering within partner pairs and country into account. Self-assessment scales, which are mostly ordinal, will be regarded as linear scales if there are at least four categories and the ‘distance’ between the categories can be regarded equal. Poisson regression or zero-inflated models may be applied to distributions resembling count or zero-inflated data. The choice of the final model will be a compromise between optimal fit and interpretability of the results for a general clinical public.

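### The primary CAIDE model adjusts for baseline only if an imbalance is judged to need it, so the covariates are not fixed in advance and the precision available from baseline CAIDE is not secured

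*Protocol article*

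**What the plan says.** Under Primary and secondary outcomes, the protocol article defines the primary effectiveness outcome as change in the CAIDE "dementia risk score between baseline and 18-month follow-up". Under Data analysis, "The effect on the CAIDE Score will be analysed using linear mixed-effect models according to the intention-to-treat principle". Clustering is handled by "taking clustering within partner pairs and country into account by testing best fit for random intercept and/or slope". The next sentence begins "If needed, we will adjust for baseline imbalances" and goes on to make allowance for clustering by centre or coach conditional in the same way. Baseline CAIDE is not named as a covariate, and nothing says when adjustment would count as needed.

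Three other places matter:

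- **Study logistics and data collection** places blood pressure, BMI, total cholesterol and physical activity at the screening visit.
- **Randomisation and blinding** places central 1:1 allocation, stratified by country, after the baseline assessments.
- **Sample size** uses the SDs of change seen in an earlier prevention trial (1.47 and 1.36), a difference of 0.186 and the settings "With 80% power, a 0.05 two-sided significance level, accounting for 21% attrition".

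The end of Data analysis refers to a full analysis plan on the registry, which is not at hand.

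**The concern.** Observed imbalance is the wrong reason to adjust in a randomised trial. Allocation is central and follows the baseline measurements, so a baseline difference between arms can only be chance. The reason to adjust is that a covariate predicts the outcome. Baseline CAIDE predicts change in CAIDE by construction, because it is subtracted to form the change.

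Two things are at stake:

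- **Precision.** If baseline CAIDE enters only when an imbalance appears, most trials run under the rule would not use it, and the variance it explains would stay in the error term.
- **Pre-specification.** With no covariate and no trigger named, an adjusted and an unadjusted primary result are both compatible with the text. The random-effects structure is also to be chosen by fit, so this adds a further open choice to a model that already has one.

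**Working it through.** **Inputs from the article (Sample size).** Difference 0.186; SDs of change 1.47 and 1.36; two-sided 0.05; 80% power; 21% attrition; planned total 2400.

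**Reproducing the plan's figure.** The pooled SD is √((1.47² + 1.36²)/2) = √2.005 = 1.416. The number per arm is 2 × (1.960 + 0.842)² × 1.416² / 0.186² ≈ 910, which is 1820 completers and 1820/0.79 ≈ 2304 in total. A t-test calculation with the SD rounded to 1.42 gives 916 per arm, 1832 completers and 1832/0.79 ≈ 2319, the stated figure. The trial was therefore sized on unadjusted change, and correctly so.

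**Power as planned.** 2400 × 0.79 / 2 = 948 completers per arm. The standard error is 1.416 × √(2/948) = 0.0650, and 0.186/0.0650 = 2.86. Power is Φ(2.86 − 1.96) = 81.6%.

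**Effect of always adjusting.** Let s be the SD of CAIDE, assumed equal at both visits, and r the correlation of baseline with final CAIDE. The variance of change is 2s²(1 − r). The residual variance given baseline is s²(1 − r²). Their ratio is (1 + r)/2. The article does not give r, so it is shown as a range with the change SD held at 1.416:

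| r (assumed) | Variance factor (1+r)/2 | Power, 948 per arm | Total N for 80% power, 21% attrition |
|---|---|---|---|
| Unadjusted | 1.00 | 81.6% | 2304 |
| 0.9 | 0.95 | 83.5% | 2190 |
| 0.8 | 0.90 | 85.4% | 2074 |
| 0.7 | 0.85 | 87.3% | 1960 |
| 0.6 | 0.80 | 89.2% | 1844 |
| 0.5 | 0.75 | 91.0% | 1730 |

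**How strongly change depends on baseline.** Under the same assumptions the correlation of change with baseline is −√((1 − r)/2). Baseline therefore explains (1 − r)/2 of the variance in change: 25% at r = 0.5, 15% at 0.7, 10% at 0.8 and 5% at 0.9. This is useful but moderate.

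**What a conditional rule recovers.** As one possible reading of the clause, a simulation with normal data and 948 per arm adjusted for baseline only when the baseline difference had p < 0.05 (4000 runs for power, 8000 for type I error):

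| r | Power, never adjust | Power, adjust if p < 0.05 | Power, always adjust | Type I error, adjust if p < 0.05 |
|---|---|---|---|---|
| 0.5 | 81.6% | 82.4% | 90.7% | 5.0% |
| 0.7 | 81.4% | 82.1% | 87.0% | 4.7% |
| 0.8 | 82.3% | 82.8% | 86.2% | 4.4% |

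The fixed trigger keeps type I error at or just below 5%, but recovers little of the gain.

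**Outer bound.** If the better of the two results could be chosen freely, the simulated type I error was 7.8%, 6.7% and 6.4% for r = 0.5, 0.7 and 0.8.

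**The case against.** Several points on the other side stand.

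- **The model is not spelled out.** The article does not say whether baseline CAIDE enters as a covariate, as a repeated outcome or not at all, and the clause could refer to other characteristics found to differ between arms. A reader might infer that the primary analysis is definitely an unadjusted change score. The text does not establish that. Nor does it remove the point: a repeated-measures model with separate arm means at baseline would not itself bring the gain. One with a common baseline mean would, but none is described.
- **The full analysis plan may fix the covariates.** It may, and the absence of a covariate list from an article is not itself a fault. The point rests only on the conditional rule that the article does state.
- **The gain may be near the lower end.** Points for sex and education do not change over the trial, which raises r. (Everyone aged 55–75 scores the same 4 points for age.) Holding the change SD at 1.416, r = 0.5 requires a CAIDE SD of 1.416/√(2 × 0.5) = 1.42. As an illustration with assumed prevalences and independent items, three 2-point items at 30% (variance 0.84 each) plus sex and activity at 50% (0.25 each) give a variance of 3.02 before education. Then r = 1 − 2.005/(2 × 3.02) ≈ 0.67 and power is about 88%.
- **Regression to the mean is a weak argument here.** A reader might infer that selection on the screening readings makes change depend strongly on baseline. Box 1 also admits people through diagnoses, medication, smoking, depression and other routes. Several entry cut-offs differ from those of CAIDE: cholesterol from 5.0 mmol/L (UK only) against above 6.5, and BMI from 28 in China against above 30. Whatever regression occurs affects both arms alike and adds noise, not bias.
- **Country is already taken into account**, so that part of the fix only settles how it enters.

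**Conclusion.** The point holds as one of efficiency and pre-specification. The article ties baseline adjustment of the primary model to observed imbalance, with no covariate and no trigger, where adjustment should rest on prognostic value decided beforehand. Always including baseline CAIDE would raise power at 2400 from 81.6% to between 83.5% and 91.0% for r from 0.9 to 0.5. Put differently, it would reduce the total needed for 80% power by about 5% to 25%. This assumes equal SDs at both visits, a change SD of 1.416 and an r that the article does not give. The gain is positive for any r below 1, and the upper figures are the favourable case.

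A reader might go on to infer that the trial is underpowered or that its type I error is inflated. Neither follows. The stated sample size reproduces and exceeds its 80% target without adjustment. A fixed p < 0.05 trigger did not inflate type I error. The 6.4–7.8% figures describe a free choice between two results, which the article leaves possible but does not plan. The change should be made, but the validity of the trial does not depend on it.

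**What to change.** Replace the conditional clause on baseline adjustment under Data analysis with:

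> The primary model includes baseline CAIDE as a fixed covariate, with country (the stratification factor), regardless of observed imbalance; any imbalance-driven adjustment is a sensitivity analysis only.

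Use the baseline value in the same way in the models for the continuous CAIDE components. If the registry analysis plan already fixes this, align the article with it and cite the place. The wording should be settled before outcome data by arm are seen.

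The cost is wording, plus a rule for the few participants with a missing baseline item, since the article itself foresees missing CAIDE items. A change score already needs the baseline value, so the covariate removes no further participants from an analysis of observed change. No new measurement is required, because the components are measured before randomisation.

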The baseline visit will be conducted face-to-face by the health coach at the GP practice or local community venue. During this visit, self-assessment questionnaires are reviewed, relevant medical history and medication use are recorded, and participants are randomly assigned to one of the treatment conditions. Only intervention participants will set a first lifestyle goal together with the coach, according to their dementia risk profile.

All participants will receive periodic adverse event (AE) questionnaires in the app, assessing incident dementia, MCI, CVD and diabetes. All self-reported outcomes will be verified with the participant’s treating physician.

After 18 months, the questionnaires and all measurements performed during the screening and baseline visit are repeated during the final visit.

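### The missing-data sensitivity analysis runs only if data missing not at random (MNAR) is not suspected, with no criterion for suspicion and no replacement named

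*Protocol article*

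**What the plan says.** Under Data analysis, the protocol article states: "The effect on the CAIDE Score will be analysed using linear mixed-effect models according to the intention-to-treat principle". On missing scores it says: "No imputation of the CAIDE Score will be done for the primary analysis". It continues: "In sensitivity analyses, we will use multiple imputation to assess the impact of missing items needed to calculate the CAIDE Score", and attaches the condition "provided there are no indications that the variables are missing not at random". The only other analysis in that sentence is that "a per-protocol analysis for those adherent to the intervention will be performed". The paragraph then adds an interaction of treatment with intervention duration, which is not a missing-data analysis.

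Under Study logistics and data collection, the follow-up is a single repeat: "After 18 months, the questionnaires and all measurements performed during the screening and baseline visit are repeated during the final visit". The COVID-19 section allows the intervention to last 12 to 18 months.

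Under Sample size, the attrition input comes from an earlier dementia-prevention trial: "Attrition after 2 years of follow-up was 21% in this study". The article also says that a full analysis plan is posted on the trial registry. That plan is not part of the material reviewed here.

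**The concern.** The condition has two faults.

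- **It is undefined.** Whether data are MNAR depends on values nobody has observed, so the trial data cannot settle it. The article gives no rule for what would count as an indication. Running or omitting the imputation is therefore a choice made with the data in hand.
- **It points the wrong way.** If MNAR is suspected, imputation is dropped and the unimputed mixed model is kept. That model also relies on ignorable missingness. An imputation model that contains the primary model's variables plus other baseline data and the items that were observed conditions on at least as much information. Grounds for distrusting the imputation are thus also grounds for distrusting the primary result, yet only the imputation is withdrawn. The per-protocol analysis does not fill the gap, because it selects further on behaviour after randomisation.

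With one follow-up measurement, a participant without a final CAIDE score adds essentially nothing to the treatment contrast. One missing item, such as cholesterol, is enough to leave the composite incomplete. The arms also differ in contact and burden (coaching, goals and reminders against a static education app), so dropout related to outcome and arm is plausible. The article gives no figure for it.

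**Working it through.** **Inputs (Sample size; Randomisation and blinding):** target difference 0.186; SDs of change 1.47 and 1.36; two-sided alpha 0.05; power 80%; attrition 21%; allocation 1:1; planned total 2400.

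**1. The plan's own figure.**
- Pooled SD = √((1.47² + 1.36²)/2) = 1.416.
- n per arm = 2 × (1.96 + 0.842)² × 1.416² / 0.186² ≈ 910, so 1820 in total.
- With attrition: 1820 / (1 − 0.21) = 2304, against 2319 stated (0.6% apart). The figure reproduces, so 21% is a genuine planning input.

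**2. Precision at the planned size.**
- Completers: 2400 × 0.79 = 1896, or 948 per arm. Missing: 2400 × 0.21 = 504.
- SE = 1.416 × √(2/948) = 0.065. Smallest significant difference = 1.96 × 0.065 = 0.1275.
- Power at 0.186 with 1896 completers: 81.6%.

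**3. Sensitivity to an MNAR departure.** Let m be the share missing in each arm and δ the amount by which intervention-arm dropouts did worse than MAR predicts. Then whole-sample effect = completer effect − m × δ. Take the completer effect as 0.186, put no departure in the control arm, and hold the SE at its completer value.
- Significance is lost at δ = (0.186 − 0.1275)/0.21 = 0.28 points (0.28/1.416 ≈ 0.2 SD).
- The effect is zero at δ = 0.186/0.21 = 0.89 points (0.89/1.416 ≈ 0.63 SD).

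The same two formulas over an assumed range of missingness, with the SE recalculated for each number of completers:

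| Missing in each arm | δ that loses significance | δ that gives zero effect |
|---|---|---|
| 10% | 0.67 | 1.86 |
| 15% | 0.42 | 1.24 |
| 21% | 0.28 | 0.89 |
| 30% | 0.17 | 0.62 |

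**4. The same departure with no true effect.** At 21% missing, δ = 0.25 gives a completer difference of 0.21 × 0.25 = 0.0525 where the truth is zero. Two-sided type I error rises from 5% to about 13%. At δ = 0.5 the bias is 0.105 and the error is about 36%.

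**The case against.** The strongest reply is that the condition has a rationale. Standard multiple imputation assumes MAR, so it would not be a valid check under MNAR, and withholding it then is not absurd. This stands. A reader might infer that the proviso removes a safeguard against informative dropout, and that striking it would restore one. Neither follows. The fault is that imputation is withdrawn with nothing put in its place, while a primary model needing a similar assumption is kept.

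Other stronger readings also go beyond the text:

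- **That the condition can never be applied.** The article asks for indications, not a test. Dropouts are asked for a short exit interview (Table 2, footnote), and reasons for leaving can inform a judgement. The criterion is undefined and subjective, but not unusable.
- **That the primary analysis is a complete-case analysis.** The article specifies a mixed model and does not say whether baseline CAIDE is an outcome or a covariate. If both time points are modelled as outcomes, inference is valid under MAR given baseline. It is still not valid under MNAR, and people without a final score still add little.
- **That the trial has no MNAR analysis.** The full analysis plan may contain one. Only the rule printed in the article can be assessed here.
- **That item-level imputation is missing.** It is already planned; only its conditional status is at issue.

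The numbers also have limits. The 0.28-point threshold partly reflects a trial with about 80% power: 0.186 is only 2.86 SEs from zero, so losing about 31% of it ends significance. The 21% was observed at 2 years, and follow-up here is 18 months or less. Participants are told only that they will get one of two lifestyle apps, and assessors are blinded. That may reduce differential dropout but does not prevent it.

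**Conclusion.** The point holds as a fault in a stated rule. The only missing-data sensitivity analysis the article describes is switched off by an undefined suspicion, with no replacement named, so the primary result can be left without a missing-data check when one is most wanted. This does not show that the primary model is wrong, that the sample size changes, or that the result will be biased.

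The tipping points of about 0.28 and 0.89 CAIDE points are illustrations. They assume a completer effect of exactly 0.186, 21% missing in each arm, the whole departure in the intervention arm, an unchanged SE and no allowance for partner clustering. They show that a modest departure of about 0.2 SD could change the conclusion on significance, whereas erasing the effect would take a considerably larger one. The condition should be corrected as a cheap improvement to a sensitivity analysis; it is not a defect that undermines the trial.

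**What to change.** - Delete the proviso and always run the planned item-level multiple imputation of the CAIDE components, separately by arm, with auxiliary baseline data in the imputation model.
- Prespecify a delta-adjusted (pattern-mixture) imputation as the MNAR analysis. Fix the range of shifts, and the arm or arms to which they apply, in advance, and report the tipping point.
- Reconcile the article's wording with the full analysis plan. If that plan already contains an MNAR analysis, refer to it in place of the condition.
- Settle this before outcome data are examined by arm, so that the choice is not driven by the data.

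The cost is some extra analysis work. No new data, visits or participants are needed, and neither the sample size nor the primary model changes.

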Participants have only access to one of two versions of the participant app. Participants randomised to the intervention condition will have access to an interactive smartphone application in their own language (English in the UK and Mandarin in China). The intervention app facilitates coach-supported self-management of seven dementia risk factors, including overweight, unhealthy diet, insufficient physical activity, smoking, hypertension, dyslipidaemia and diabetes. Participants can set personal goals for lifestyle change, following the specific, measurable, achievable, realistic and time-bound principle. Participants receive automated reminders to enter measurements (eg, number of steps and blood pressure) for these goals, facilitating progress monitoring. The intervention participants will receive support from an experienced lifestyle coach, who is trained in motivational interviewing and works according to a coach protocol based on current guidelines for risk factor management. Regular training sessions in each country will enhance uniformity in coaching procedures, taking cultural differences into account. During the baseline visit, after randomisation, the coach discusses the participant’s dementia risk profile, and a first lifestyle goal will be set through the app. After the baseline visit, all communication between the participant and coach will take place through the messaging functionality. Through the coach portal, the coach can view goals and measurements, send tailored education modules, and offer remote support to facilitate sustainable behaviour change.

Participants randomised to the control condition will have access to the control app, which is similar in appearance but only contains education material, lacking interactive features and coach-support. During the baseline visit, control participants will receive concise feedback on their risk profile.

The PRODEMOS intervention in its current design is positioned as add-on to existing care.

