	Acceptability	Short questionnaire of agreeability, user-friendliness, credibility	Intervention participants, coaches	After 3 months and at study end
	Sustainability	Adherence, dropout	Intervention participants, dropouts†	Throughout the study
	Cost	Implementation costs	N.A.	N.A.
Qualitative	Feasibility	The extent to which the mHealth intervention can be carried out →practical and social barriers/facilitators	Intervention participants, dropouts,† coaches	After 3 months and at study end
	Appropriateness	Perceived fit or relevance in the target population	Intervention participants, dropouts,† coaches	After 3 months and at study end
	Acceptability	Agreeability, user-friendliness, credibility	Intervention participants, dropouts,† coaches	After 3 months and at study end
	Fidelity	Degree to which the mHealth application is implemented compared with the original protocol	N.A.	After the study

*For all analyses, a Chinese and UK population will be involved.

†Study dropouts will be asked to participate in a short exit interview.

mHealth, mobile health.

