### Pilot study

Between December 2019 and March 2020, a 6-week pilot study was conducted in the Brighton and Sussex area, the UK. Since the main aim was to test study logistics and functionality of the intervention app, participants were randomised in a 3:1 (intervention/control) ratio. An invitation letter was sent to 600 potentially eligible patients from two GPs. The response rate was 14.8% (n=89), of whom 21 participants (3.5%) could be included. The main reasons for exclusion were not living in the designated postal code area and having <2 dementia risk factors. Participants had a median age of 69 years old, and 12 (57%) were men. Fifteen participants were allocated to the intervention group and six to the control group.

During the pilot study, 10 of 15 intervention participants set at least one goal (range: 1–8 goals). Goals were set in five domains, including physical activity, healthy diet, body weight, blood pressure and cholesterol. Six of ten participants entered goal-related measurements (range: 2–243 measurements). All intervention participants used the chat functionality to consult the coach. In total, 278 messages were sent back and forth, that is, on average three messages per intervention participant per week.

The pilot study was evaluated through qualitative sessions with the participants and coaches. The main adjustments based on the participants’ feedback included improvements to the chat functionality (allowing attachments and larger font size), simplification of the functionality to enter and view measurements, setting the first goal together with the coach and more detailed instructions for app use through an instruction video and written manual. Based on feedback from the coaches, we improved the functionalities for population management in the coach portal, including an input screen to make notes about individual participants and a functionality to send education material to (groups of) participants.

A similar pilot study will be conducted in China, to test platform functionality and study logistics in all seven participating trial centres.

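### The per-protocol sensitivity analysis selects on post-randomisation adherence that, as described, has no control-arm equivalent, so it can show benefit where there is none

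*Protocol article*

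**What the plan says.** The Data analysis section makes intention-to-treat primary: the CAIDE score is to be "analysed using linear mixed-effect models according to the intention-to-treat principle". Among the sensitivity analyses it adds that "a per-protocol analysis for those adherent to the intervention will be performed". The article names no control-arm criterion for that set and no adjustment for who ends up in it.

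Three other places bear on what adherence can mean:

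- Intervention and control condition: the control app "only contains education material, lacking interactive features and coach-support".
- Table 2, Sustainability row: the measurement is "Adherence, dropout", and the population is intervention participants and dropouts. Control participants are not listed.
- Data analysis, subgroups: the trial records "willingness to change lifestyle (assessed with one question during the baseline visit". This item is listed as a subgroup factor and not as an adjustment in the per-protocol analysis.

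**The concern.** People who keep using a self-management app for up to 18 months have selected themselves. They may well be the ones who would have improved their blood pressure, weight or activity anyway. The control arm contains the same kind of people, but they cannot be picked out by the same behaviour because their app offers no goals, measurements or coach contact. Restricting one arm and not the other gives up the balance that randomisation provided.

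What is at stake is interpretation. The planned effect is small relative to its spread (0.186 points, SD about 1.4), so modest selection can produce a difference of similar size. A neutral intention-to-treat result beside a positive per-protocol result would invite the claim that the app works if used, which this comparison cannot support. Nor does it test the robustness of the intention-to-treat estimate, since it estimates something different.

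**Working it through.** **Inputs from the article.** Target difference 0.186; SD of change 1.47 and 1.36; two-sided alpha 0.05; power 80%; attrition 21%; required N 2319, raised to 2400 (Sample size). Allocation 1:1 (Randomisation and blinding).

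**The plan's own figure.** Pooled SD = √((1.47² + 1.36²)/2) = 1.416. This gives 910 per arm, 1820 in total, and 1820/0.79 = 2304. That is within 1% of the stated 2319, so the inputs are sound. The sample size itself is not in question here.

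**Bias under a true null.** Let p be the adherent share of the intervention arm and g the extra fall in CAIDE that adherers would show over non-adherers with no treatment effect. With no effect, the whole intervention arm has the same expected change as the control arm, m. Since m = p × (adherer mean) + (1 − p) × (non-adherer mean), the adherers lie (1 − p) × g below m. That is the expected bias of adherers against all controls. Under intention-to-treat, the bias from this source is 0.

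**Values used.** The pilot (Pilot study section) shows that engagement varies: "10 of 15 intervention participants set at least one goal" (10/15 = 0.67), and "Six of ten participants entered goal-related measurements" (6/15 = 0.40). I add 0.80 as a more favourable case. The article gives no value for g; 0.1 to 0.4 is an assumption.

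**False-positive probability.** Normal approximation with 2400 × 0.79/2 = 948 completers per arm, 948 × p adherers, and SE = 1.416 × √(1/948 + 1/(948p)). Each cell shows bias in CAIDE points and the two-sided probability of significance, which is nominally 5%.

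| p | g = 0.1 | g = 0.2 | g = 0.3 | g = 0.4 |
|---|---|---|---|---|
| 0.40 | 0.06; 11% | 0.12; 29% | 0.18; 55% | 0.24; 80% |
| 0.67 | 0.03; 7% | 0.07; 15% | 0.10; 28% | 0.13; 45% |
| 0.80 | 0.02; 6% | 0.04; 9% | 0.06; 14% | 0.08; 21% |

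The bias runs from 0.02/0.186 = 11% to 0.24/0.186 = 129% of the target. A spurious effect equal to the target needs g = 0.186/(1 − p): 0.31, 0.56 or 0.93 for p = 0.40, 0.67 or 0.80.

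**Check on the alternative estimator.** With randomisation as the instrument and no access to the intervention app among controls, the complier-average estimate is the intention-to-treat difference divided by p. It is 0 when the intention-to-treat effect is 0, whatever g is. If non-adherers gain an effect d from partial exposure, the estimate is too large by ((1 − p)/p) × d: 1.5d at p = 0.40 but 0.25d at p = 0.80. Its SE is about 1.416 × √(2/948)/p = 0.065/p, that is 0.16 at p = 0.40 and 0.08 at p = 0.80. The per-protocol SEs are 0.09 and 0.07.

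**The case against.** The strongest reply is that one clause in a journal article is being read closely. The comparator is not spelled out. The article says that the full analysis plan is published on the trial registry, and an adherence definition, a control-arm rule or an adjustment may stand there. This is fair: the absence of those details here is not the finding, and use of the whole control arm is an inference from the wording. What remains is that the selection variable is named, and a threshold built on goals, measurements or coach messages cannot be matched in controls, who have none.

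Several stronger readings are tempting, and the article does not support them:

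- *Adherence cannot be observed at all in controls.* Too strong. The Figure 1 legend says that the control app has similar links to the database, and education items read are among the user statistics. Some use may therefore be logged in both arms, though Table 2 lists adherence for the intervention side only.
- *The pilot shows that a third will not engage.* The pilot had 5 of 15 setting no goal, but all 15 used the chat, and the first goal is now set with the coach at the baseline visit. The pilot shows that engagement varies and depends on the criterion. It does not predict the trial's adherent share.
- *The analysis is certain to favour the intervention, by about the target effect.* Both size and direction rest on g. A gap of 0.3 to 0.4 exceeds the mean change of −0.290 in the intervention arm of the earlier trial cited for the sample size, and the low end of the table is nearly harmless.
- *The trial's main conclusion is at risk.* It is not. Intention-to-treat is primary, and the article nowhere says that a per-protocol result will support an effectiveness claim.

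One objection to the remedy also stands. Every intervention participant has a coach session and sets a first goal at baseline, so those below any later threshold are partly treated and the exclusion restriction holds only approximately.

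**Conclusion.** The point holds as a defect in a sensitivity analysis. As described, the analysis selects on behaviour after randomisation in one arm. If adherers are then set against the control arm, the result is a non-randomised contrast that can show benefit under a true null.

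The size is conditional: about 0.02 to 0.24 CAIDE points, with a false-positive probability of about 6% to 80% instead of 5%, for p of 0.40 to 0.80 and g of 0.1 to 0.4. This assumes that the comparator is the whole control arm, that adherers have the better prognosis, and that the SD and attrition match the planning values. The possibility of a spurious benefit follows from the design of the comparison; its magnitude does not follow from anything in the article.

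**What to change.** Make a complier-average causal effect analysis the adherence analysis:

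- Use randomisation as the instrument (two-stage least squares), with baseline CAIDE and country as covariates and clustering by couple.
- Set the adherence threshold in advance from the app logs and keep it lenient, so that few partly treated people count as non-adherent. Repeat with other thresholds.
- State that the exclusion restriction is only approximate, because all intervention participants receive the baseline coach session and a first goal.

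If the per-protocol analysis is kept, adjust or weight it for baseline CAIDE, country and the willingness-to-change item already collected. Label it as a non-randomised comparison, and say in advance that it will not be used to support effectiveness when intention-to-treat is neutral. Adjustment reduces the selection bias only as far as those variables capture it.

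The cost is a little more analysis work on user data that the trial already plans to collect, a wider confidence interval than the per-protocol analysis would give, and an assumption that has to be stated and defended.
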